## Methods

### Research objectives

1. To investigate the predictive relationship between change in objectively measured PA levels in a cohort of patients with acute (< 6 weeks' duration) LBP [54] from baseline to 3 months, and change in functional outcome at 3 months and recovery over a 1 year period.

2. To assess the effect of occupation and occupational activity levels, personal factors, pain levels, functional status and psychosocial profile on the relationship between PA levels and LBP outcomes at 3 months and at 1 year.

3. To determine the relationship between restoration of "normal" levels of PA as considered by the patient and functional recovery.

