### Hypotheses

Three specific hypotheses will be tested:

1. Positive changes in PA levels of participants with acute LBP (from baseline to 3 months) are a positive predictor of recovery (defined from change score in *Roland Morris Disability Questionnaire*) [54] at 3 months and at 1 year;

2. Psychosocial factors including levels of fear avoidance beliefs, depression and anxiety and occupational factors including types of occupation and levels of manual or sedentary work act as confounders in the relationship between activity change and the course of LBP over a 1 year period;

3. Restoration of "normal" levels of PA at baseline and at 3 months is a positive predictor of functional recovery over a 1 year period.

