## Analyses

Multiple linear regression will be used to investigate the associations of the main predictor variable, change in RT3 VM counts/hour/week (ΔRT3) from baseline to 3 months, with the main outcome variable change in functional outcome (ΔRMDQ). The change score will be calculated by subtracting each participant's 3 month RMDQ score from their baseline RMDQ score. Unadjusted and adjusted analyses will be performed. Adjusted analyses will include the following variables, shown to be putatively associated with both PA and functional recovery in LBP: age, gender, occupation, baseline pain level (pain questionnaire), functional status (baseline RMDQ) and baseline measurements of depression, anxiety, emotional distress and fear avoidance (GHQ12 and FABQ). We plan to analyze each of the explanatory variables univariately initially to assess the relationship with the dependant variable (RMDQ change). We will include factors in the model which in univariate analyses have a *p*-value < 0.10. The significant explanatory variables contained in the separate models will then be combined and re-examined using further modeling. We plan to use multiple linear regression to assess which of the included explanatory variables and/or their interactions with PA change predict change in RMDQ. For those variables which remain in the final model, an examination of their significance (p < 0.05) will be undertaken to evaluate their contribution to the final model.

At 1 year the relationship between ΔRT3 and presence or absence of on-going low back pain (Y/N) from the modified Nordic LBP questionnaire will be investigated using logistic regression. At 1 year the relationship between the BPAQ change score from baseline (pre-LBP) to BPAQ score at 1 year (ΔBPAQ) with the outcome of on-going LBP (Y/N) will also be explored using logistic regression.

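### Hypothesis 2 concerns confounding, but the Analyses section screens covariates at univariate p < 0.10 and judges them and their interactions at p < 0.05, which does not measure confounding

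*Protocol article*

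**What the plan says.** All references are to the protocol article.

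- **Hypotheses, item 2:** fear avoidance beliefs, depression, anxiety and occupational factors "act as confounders in the relationship between activity change and the course of LBP over a 1 year period".
- **Research objectives, item 2** is looser: it asks about the effect of these factors "on the relationship between PA levels and LBP outcomes at 3 months and at 1 year".
- **Analyses, models:** "Unadjusted and adjusted analyses will be performed". The adjusted analyses are said to contain "age, gender, occupation, baseline pain level (pain questionnaire), functional status (baseline RMDQ) and baseline measurements of depression, anxiety, emotional distress and fear avoidance", a set described as "shown to be putatively associated with both PA and functional recovery in LBP".
- **Analyses, selection:** each explanatory variable is first tested alone against RMDQ change. "We will include factors in the model which in univariate analyses have a *p*-value < 0.10". The combined model is then used to "assess which of the included explanatory variables and/or their interactions with PA change predict change in RMDQ".
- **Analyses, final criterion:** for the variables that remain, "an examination of their significance (p < 0.05) will be undertaken to evaluate their contribution to the final model".
- **Analyses, 1 year:** ongoing back pain (yes/no) is related to ΔRT3 by logistic regression. No covariates are named.

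**The concern.** A factor confounds the relation between activity change and recovery to the extent that the ΔRT3 coefficient moves when the factor is adjusted for. The criteria by which the plan judges factors are different: association with ΔRMDQ alone (the screen), association with ΔRMDQ given the other terms (p < 0.05), and variation of the ΔRT3 slope across levels of the factor (interaction, that is, effect modification). None of these uses the factor's relation to activity change in the way that confounding requires.

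Two things are at stake. Hypothesis 2 could be declared supported or refuted on p-values that do not bear on it. And because the screen looks only at the outcome, a real confounder can be removed before the adjusted ΔRT3 estimate is computed. The screen also conflicts with the statement, a few lines earlier, that the adjusted analyses contain the whole listed set.

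**Working it through.** The plan gives no figure on this point, so there is none to reproduce. The check is algebra plus a simulation under stated assumptions.

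**Inputs from the protocol article.** 65 evaluable participants and about 120 recruited (Sample size and statistical power; taken as stated). Screen at 0.10 and final criterion at 0.05 (Analyses). The adjustment set has 9 named items, or 7 if GHQ12 and FABQ each give one score.

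**Assumptions, not from the document.** One covariate C and activity change PA, both with SD 1 and correlation r. Outcome = b_PA × PA + b_C × C + error with SD 1. 6,000 runs per case.

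**What each quantity measures.**

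- Unadjusted PA slope = b_PA + r × b_C. Adjusted PA slope = b_PA. Confounding is the difference, r × b_C.
- The p < 0.05 test in the joint model tests b_C. It does not ask whether r differs from 0.
- The univariate screen tests b_C + r × b_PA, which can be near 0 although r × b_C is large.

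**Results at N = 65.**

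| Case | r | b_C | b_PA (true) | Unadjusted PA slope | Slope seen by screen | Passes p < 0.10 | C has p < 0.05 in joint model | Mean PA slope after screen |
|---|---|---|---|---|---|---|---|---|
| A: prognostic, not a confounder | 0 | 0.5 | 0.30 | 0.30 + 0 = 0.30 | 0.5 + 0 = 0.50 | 98% | 97% | 0.30 |
| B: creates a spurious effect | 0.5 | 0.3 | 0 | 0 + 0.15 = 0.15 | 0.3 + 0 = 0.30 | 76% | 52% | 0.02 |
| C: masks part of the effect | 0.5 | −0.4 | 0.50 | 0.50 − 0.20 = 0.30 | −0.4 + 0.25 = −0.15 | 29% | 76% if entered | 0.37 |
| D: screen is blind to it | 0.6 | 0.3 | −0.50 | −0.50 + 0.18 = −0.32 | 0.3 − 0.30 = 0 | 10% | 47% if entered | −0.34 |

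In case A the factor is almost always significant and confounds nothing. In case B it accounts for the whole apparent effect and is significant about half the time. In cases C and D the screen usually discards the confounder and leaves most of the bias. In case C, power for ΔRT3 is 76% after screening against 92% with full adjustment.

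**Range at N = 120.** In case B, significance rises to 80% although the confounding is still 0.15, so the verdict follows sample size and not confounding. In case C the factor passes the screen in 44% of runs (mean slope 0.40). In case D it passes in 10% (−0.34).

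**False flags under the planned sequence.** Here nothing predicts the outcome, there are 7 to 9 independent candidates, N = 65 and 4,000 runs. At least one covariate or interaction is falsely flagged in 28% to 36% of runs. Covariates alone account for 27% to 34%, and interactions for 3% to 5%.

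**1 year.** Hypothesis 2 runs over one year. The ΔRT3 logistic model names no covariates, so as written it yields no adjusted coefficient to set against the unadjusted one.

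**The case against.** The strongest reply is that the right ingredients are already in the plan. Unadjusted and adjusted analyses are both promised, and the listed set rests on association with both activity and recovery, a sound ground for choosing confounders. The comparison of the two ΔRT3 coefficients may be spelled out in a fuller document. The selection steps might also be a separate predictive exercise that leaves the fully adjusted model intact.

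Much of this stands. A reader might infer that the plan never produces the quantity hypothesis 2 needs, and that is too strong. What remains is that the article does not merely stay silent. It fixes a selection rule and a p-value criterion, ties neither to a separate purpose, and calls the screened result the final model.

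A reader might also infer that the interactions have no place. Objective 2, and the abstract's aim of seeing whether these factors affect the relationship, can fairly be read as effect modification, which interactions address. The mismatch is only with the word confounders in hypothesis 2.

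A third tempting inference is a large risk of chance interactions: with 7 to 9 tests, 1 − 0.95^7 = 30% to 1 − 0.95^9 = 37%, in models of 1 + 7 + 7 = 15 to 1 + 9 + 9 = 19 terms. The document does not support this, because interactions are examined only for included variables and the p < 0.10 screen leaves few of those. The simulated figure is 3% to 5%.

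Nor do the checks show that the ΔRT3 test itself is badly inflated. In case B the screened model rejected a true null in 5.2% of runs, against 4.8% fully adjusted and 21.8% unadjusted.

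**Conclusion.** The point holds in a limited form. For hypothesis 2, the stated criteria (outcome-only screening, p < 0.05, interactions) do not measure confounding. The screen can remove real confounders, and it contradicts the promise of a fixed adjustment set. The planned unadjusted and adjusted models are the right basis, but the plan does not say that their ΔRT3 coefficients will be compared, and at 1 year there is no named adjustment at all.

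The algebra does not depend on the simulation. The sizes do: they rest on assumed correlations of 0 to 0.6, assumed slopes, one covariate at a time in cases A to D, and mutually independent covariates in the false-flag check. The real values are unknown, and the bias from screening ranges from negligible (case B, 0.02) to most of the confounding (case D, 0.16 of 0.18). The main harm is a wrong answer to hypothesis 2. Multiplicity is secondary and comes mostly from the covariate tests.

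**What to change.** 1. For hypothesis 2, fit the pre-specified adjustment set without p-value screening. Using the same participants in every model, report the ΔRT3 coefficient with its 95% CI (a) unadjusted, (b) with the psychosocial block added (GHQ12, FABQ), (c) with the occupational block added and (d) fully adjusted. Take the change in the coefficient, with its own CI (for example by bootstrap), as the measure of confounding.
2. Say which variables form the occupational block. The adjustment list names only occupation, while the sections on the research protocol and its measures also call the manual/sedentary item and occupational activity (the BPAQ work index) potential confounders.
3. Do the same for the 1-year ΔRT3 logistic model as far as events allow. With 65 participants the rarer outcome has at most 32, so blocks may have to be entered one at a time. An odds ratio can shift on adjustment without confounding, so show the change on a standardised risk scale too.
4. Keep interactions for Objective 2 if wanted, limited to a few named in advance and labelled exploratory effect modification.
5. If the screened model is kept, call it an exploratory prediction model and state that it does not answer hypothesis 2.

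**Cost:** wording and a little extra analysis, with no new data. The unscreened model carries more terms (ΔRT3 plus 7 covariates if each item is one term, more if occupation has several categories), which costs some precision at about 65 evaluable participants.

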### Research protocol and timetable

At an initial visit each participant's weight, height, age, sex, occupation and ethnicity will be recorded. Occupation coding will be carried out according to Australian and New Zealand Standard Classification of Occupations [56]. Also recorded, whether the participant is working or off-work due to the current LBP episode, the number of days of the week and total average hours that each participant works, and whether the participant considers their work to be either manual or sedentary. This occupational information will be used to provide a baseline descriptive account of the group, and also included as a potential confounder in the relationship between PA and functional recovery.

Participants will complete a number of validated functional LBP outcome measures at baseline [57]. The primary outcome measure is the RMDQ, accepted as a valid and sensitive measure of condition-specific functional outcome in LBP populations [58], and considered as the preferred instrument for assessing change in function over time in LBP [59]. Secondary outcomes will be the *Visual Analogue Scale *(VAS) measure of pain over the past 7 days which has been shown to be a valid and reliable clinical measure of pain in LBP populations [60] and a specific activity question developed for this study which asks the participant whether they have returned to full "normal' activities since the episode of low back pain (Y/N).

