At 1 year each participant will be sent the following questionnaires: VAS, FABQ, RMDQ, the BPAQ, GHQ12 and a modified Nordic LBP Questionnaire [73] with a self return envelope. The Nordic LBP Questionnaire has been previously employed as a measure of LBP recovery in an occupational setting [74] and as a measure of incident LBP, for assessing the associations between physical activity and incidence of LBP [75]. The BPAQ will be used to record current levels of PA at the 1 year point. The estimated duration of the study will be approximately two years to complete recruitment and 1 year follow-up (Figure 1).

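### Hypothesis 1 defines 1-year recovery by RMDQ change, but the only 1-year models stated use a yes/no pain outcome

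*Protocol article*

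**What the plan says.** Four places in the protocol article bear on this.

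- **Hypotheses.** Hypothesis 1 says that positive changes in physical activity "are a positive predictor of recovery (defined from change score in *Roland Morris Disability Questionnaire*) [54] at 3 months and at 1 year". The instrument and both time points are fixed there.
- **Research protocol and timetable.** "The primary outcome measure is the RMDQ". Pain on the VAS and the question on return to normal activities are secondary.
- **Physical activity measurement.** "At 1 year each participant will be sent the following questionnaires: VAS, FABQ, RMDQ, the BPAQ, GHQ12", together with the modified Nordic questionnaire. The RMDQ is thus available at 1 year.
- **Analyses.** The main model is a multiple linear regression of ΔRMDQ on ΔRT3, where ΔRMDQ is the baseline score minus the 3-month score. For 1 year there are two logistic regressions. The first concerns "At 1 year the relationship between ΔRT3 and presence or absence of on-going low back pain (Y/N) from the modified Nordic LBP questionnaire". The second relates change in the Baecke score to the same yes/no outcome. No other 1-year analysis is described.

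**The concern.** A hypothesis listed for testing names its outcome and its times, and the section that says how it will be tested uses another outcome at one of those times. Presence of back pain and functional recovery are different constructs. A participant may still report some pain with little disability, or improve greatly on the RMDQ without being free of pain. The article itself separates the two, with function as primary and pain intensity as secondary.

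Two things are at stake. A 1-year result on ongoing pain would not answer the question that Hypothesis 1 asks at 1 year. And with the hypothesis naming one 1-year outcome and the analysis naming another, the choice of which to report as the test could be made after the results are known.

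**Working it through.** No figure is in dispute, so the check is a comparison of sections.

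1. **Outcome required by Hypothesis 1.** RMDQ change score, at 3 months and at 1 year.
2. **Data collected.** RMDQ at baseline, at the end of week 12 and at 1 year. Both change scores, baseline to 3 months and baseline to 1 year, can be formed.
3. **Outcome analysed at 3 months.** Baseline RMDQ minus 3-month RMDQ, by linear regression on ΔRT3. This matches the hypothesis.
4. **Outcome analysed at 1 year.** Ongoing low back pain, yes or no, by logistic regression on ΔRT3 and, separately, on ΔBPAQ. This does not match the hypothesis. The 1-year RMDQ score enters neither model, and the only definition given for the change score excludes it.
5. **Count.** Hypothesis 1 names two time points. One has a stated model on the defined outcome and one does not.
6. **Reach.** The Sample size and statistical power section is built on the RMDQ change from baseline to three months (a difference of 4 points, standard deviation 5.4, 65 participants before allowing for loss). Nothing in that calculation depends on the 1-year outcome, so neither it nor the 3-month model is touched by this point.

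A companion check on Hypothesis 3: it holds that restored normal activity "is a positive predictor of functional recovery over a 1 year period". The activity question is asked at the end of week 12 and the RMDQ is collected at 1 year, so predictor and outcome both exist, but Analyses lists no model that joins them. Nothing in Analyses conflicts with Hypothesis 3. The model is simply not listed.

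**The case against.** The strongest defence is that the 1-year choice was deliberate. Research objective 1 separates "change in functional outcome at 3 months and recovery over a 1 year period" and names no instrument for the second part. The article also notes that the Nordic questionnaire has served as a measure of recovery from back pain, and the Discussion looks ahead to recovery and recurrence at 1 year. On that reading the Analyses section fits the objective, and the fault is one loose phrase in Hypothesis 1. A binary outcome might even be practical if many participants have little disability left by 1 year.

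This explains the choice and stands as far as the objective goes. It does not reconcile the choice with Hypothesis 1, which names the RMDQ at 1 year. Nor is this detail left to a fuller document: the article does specify predictor, outcome, instrument and model for 1 year, and they differ from the hypothesis.

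Some stronger readings that a reader might infer are not supported:

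- **That the 1-year RMDQ will never be analysed.** The full protocol or analysis plan is not shown and may contain such a model. The point concerns what this document states.
- **That the 1-year models are unadjusted.** The article repeats no covariate list for them, but it does not call them unadjusted. Objective 2 and Hypothesis 2 both extend the study of confounding factors to 1 year.
- **That a definite share of information is lost.** The usual formula for dichotomising a normal outcome does not apply, because the Nordic item is not a cut of the RMDQ, and the documents give no expected proportion with ongoing pain.
- **That Hypothesis 3 is contradicted.** An unlisted model in a condensed article is an omission, and a minor one here.

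**Conclusion.** The point holds in a limited form. Hypothesis 1 and the Analyses section disagree on the 1-year outcome, and the disagreement concerns the declared primary measure. As written, the 1-year part of Hypothesis 1 is not tested on its own defined outcome. A result on ongoing pain could sit beside that test but could not replace it.

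Its size is one time point of one hypothesis. A reader might infer that the study's main result is compromised. It is not, since the main outcome and the power calculation both rest on 3-month RMDQ change. The conclusion assumes only that the article's hypotheses and analyses are both meant as current text; it rests on no numerical assumption.

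**What to change.** In Analyses, name as the 1-year test of Hypothesis 1 a linear regression of 1-year RMDQ (or of baseline-to-1-year change) on ΔRT3, adjusted for baseline RMDQ and the covariates of the 3-month model. Keep the logistic model on the Nordic yes/no item as a named secondary analysis.

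If the investigators do intend ongoing pain to be the 1-year outcome, the alternative is to restate the 1-year part of Hypothesis 1 in those terms. Either change should be made before the 1-year data are examined.

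As a minor addition, list a model for Hypothesis 3: the 1-year RMDQ outcome regressed on the 3-month answer about return to normal activities. Whether to adjust for baseline or for 3-month RMDQ is for the analysts to decide and state. Adjusting for the 3-month score removes recovery already achieved by then, so the two answer different questions.

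The cost is one or two extra regressions and a few sentences of analysis text. No new data collection is needed, and the sample size calculation stays as it is.

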### Physical activity measurement

All RT3 monitors will undergo testing prior to field use as part of the standardised protocol recommended when employing accelerometry measurement [69,70]. Previous research has shown high levels intra-monitor variability [49] and therefore each participant will be required to use the same RT3 monitor at baseline and 3 months. Field practice of monitor use and monitor placement will be standardised by asking the participants to wear the RT3 monitor on the right hip for all waking hours; to report wear times and reason for removal; to note the days that they work; and also to report sleep patterns [70] and hourly activities in an activity diary over the week [53].

The dimensions and specifics of the RT3 have been reported previously [49]. The RT3 triaxial accelerometer stores accumulated activity counts, derived from the three axes ([X^2 ^+ Y^2 ^+ Z^2^]^0.5^) to calculate a summed VM. Mode 4 will be employed for this study, which stores accumulated activity counts every second and calculates an average VM for each one-minute epoch over the 7 days of monitoring. Previous research has validated the use of RT3 VM counts as a measure of free living activity and energy expenditure [50].

Participants will be contacted twice during this week by text and/or phone to improve compliance in wearing the RT3, recording activity in the activity dairy, and to address any problems the participants might be having with either the RT3 or in using the activity diary. At the completion of the week the RT3 data will be downloaded to a portable computer and each participant will complete a 7-day recall questionnaire (7D-PAR) [71,72]. The 7D-PAR provides an estimate of the average total daily energy expenditure (TDEE) and physical activity energy expenditure (PAEE) for each participant.

All participants will be sent a reminder letter between the first and second period of monitoring; further contact will be made approximately 1 week prior to their scheduled date for re-monitoring at the 3-month point. Each participant will then repeat the activity monitoring procedure as per the baseline. At completion of week 12 each participant will be asked to complete the RMDQ, VAS and simple activity question and in addition an RT3 utility questionnaire developed for this study. This will assess any specific utility issues of PA measurement within this patient population.

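### The two 1-year logistic models name no covariates, although Objective 2 and Hypothesis 2 require confounders to be addressed at 1 year

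*Protocol article*

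**What the plan says.** **Aims that reach to 1 year.** Under Research objectives, Objective 2 will assess the effect of occupation, personal factors, pain, function and psychosocial profile "on the relationship between PA levels and LBP outcomes at 3 months and at 1 year". Under Hypotheses, Hypothesis 2 states that psychosocial and occupational factors "act as confounders in the relationship between activity change and the course of LBP over a 1 year period".

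**Adjustment at 3 months.** The first paragraph of Analyses concerns the linear regression of ΔRMDQ on "change in RT3 VM counts/hour/week (ΔRT3) from baseline to 3 months". It says "Unadjusted and adjusted analyses will be performed" and lists the covariates: age, gender, occupation, baseline pain, baseline RMDQ, GHQ12 and FABQ. It then describes univariate screening to "assess the relationship with the dependant variable (RMDQ change"), followed by joint modelling with interactions.

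**Models at 1 year.** The next paragraph has two logistic regressions. One concerns "At 1 year the relationship between ΔRT3 and presence or absence of on-going low back pain (Y/N) from the modified Nordic LBP questionnaire". The other takes ΔBPAQ "with the outcome of on-going LBP (Y/N) will also be explored using logistic regression". Each has one activity predictor, and neither mentions a covariate.

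**Data available.** Occupational data, pain, RMDQ, FABQ and GHQ12 are collected at baseline. Physical activity measurement adds: "At completion of week 12 each participant will be asked to complete the RMDQ, VAS and simple activity question".

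**The concern.** This is an observational cohort, so an association between activity change and later pain can be interpreted only after confounders are dealt with. The article accepts this and makes it a hypothesis with a 1-year horizon, but the analysis section carries it out only for the 3-month outcome. Two things are at stake:

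- **Confounded 1-year estimates.** Someone with worse baseline function, more fear avoidance or a more manual job may differ both in activity change and in the chance of still having pain at 1 year. A one-predictor odds ratio mixes these influences with any role of activity.
- **An untested hypothesis.** Whether a factor confounds an association is judged by comparing the activity coefficient with and without that factor. No such comparison is stated at 1 year.

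A further issue applies to ΔRT3 only. It spans the same baseline-to-3-month window as the recovery measured by ΔRMDQ. If people who recover by week 12 move more and also have less pain at 1 year, ΔRT3 will be associated with the 1-year outcome even if activity does nothing. ΔBPAQ runs from before the episode to 1 year, so this argument does not carry over to it.

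**Working it through.** The article gives no figure for the 1-year models, so there is none to reproduce. Its sample size of 65 belongs to the 3-month comparison.

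**1. Aims against analyses**

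| Element | 3 months | 1 year |
|---|---|---|
| Objective 2 | yes | yes |
| Hypothesis 2 | within the horizon | yes |
| Adjusted analysis stated | yes, for ΔRMDQ | none stated |
| Covariates listed | seven | none |
| Screening and interactions | yes, for ΔRMDQ | none stated |

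**2. How much adjustment the data can bear**

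Inputs: about 120 recruited and 40-50% attrition (Sample size and statistical power); share still in pain at 1 year 30-60% (assumption; not in the documents).

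- Completers: 120 × (1 − 0.5) = 60 to 120 × (1 − 0.4) = 72.
- Rarer outcome group = n × min(p, 1 − p): lowest 60 × 0.30 = 18, highest 72 × 0.50 = 36.
- ΔRT3, the seven listed covariates and 3-month RMDQ make at least 9 terms (occupation counted once): 18/9 = 2.0 to 36/9 = 4.0 events per term.
- A short model with activity, baseline RMDQ, FABQ, GHQ12 and occupational activity has 5 terms: 18/5 = 3.6 to 36/5 = 7.2.
- With 3-month RMDQ added, 6 terms: 18/6 = 3.0 to 36/6 = 6.0.

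Copying the whole 3-month procedure to 1 year would overload the model. A short set is just workable with penalisation.

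**3. Could 3-month status matter for ΔRT3?**

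Illustrative simulation: n = 65, 1000 runs per setting, two-sided 0.05, no ΔRT3 effect given 3-month status. Assumed inputs are the correlation of ΔRT3 with recovery and the odds ratio (OR) of 3-month status for 1-year pain. ORs in the table are medians per SD of ΔRT3.

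| Correlation | Status OR | Unadjusted: OR, rejections | With 3-month status: OR, rejections |
|---|---|---|---|
| 0.2 | 4 | 0.89, 7.5% | 0.99, 5.1% |
| 0.2 | 8 | 0.86, 8.4% | 1.00, 5.1% |
| 0.3 | 4 | 0.84, 8.7% | 0.99, 5.6% |
| 0.3 | 8 | 0.80, 13.8% | 0.99, 3.5% |
| 0.5 | 4 | 0.75, 18.1% | 1.02, 5.3% |
| 0.5 | 8 | 0.66, 31.3% | 1.00, 4.1% |

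A second simulation used a continuous score: logit P(pain at 1 year) = −1.5 + 0.25 × 3-month RMDQ, 44% prevalence, activity-RMDQ correlation −0.27 or −0.38, no activity effect. The OR per SD of ΔRT3 was 0.86 / 0.81 unadjusted, 0.78 / 0.69 adjusted for baseline RMDQ alone, and 1.01 / 1.01 with 3-month RMDQ added. Rejections at n = 65 were 9% / 12%, 15% / 26% and about 5%. Baseline adjustment alone therefore does not remove this particular distortion, and here it enlarged it.

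**4. The opposite causal structure**

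With the same outcome model and an assumed RMDQ distribution, let activity act on 1-year pain only by improving 3-month RMDQ, by 1 / 1.5 / 2 points per SD. In 200,000 records the unadjusted OR was 0.84 / 0.76 / 0.70. Adding 3-month RMDQ moved it to 1.00 each time. A true total effect disappears in the same way as a spurious one.

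**The case against.** **Silence is not a decision.** The article never says that the 1-year models are unadjusted. A condensed article may leave a secondary model's covariates to the full plan, and the intent to treat occupational and psychosocial data as potential confounders appears under Research protocol and timetable. This stands as far as wording goes: the models name no covariates, which is not proof that none will be used. It does not remove the mismatch. The article spells out adjustment at 3 months and then describes the 1-year models without it, against its own objective and hypothesis. The sentence promising adjusted analyses sits in the ΔRMDQ paragraph, and the steps that follow it are tied to RMDQ change.

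**ΔRT3 as a mere marker of recovery.** A reader might infer that ΔRT3 simply stands in for who had already recovered, so that the unadjusted model would show a protective effect that does not exist. The documents do not support this. That result is built into simulations that assume no activity effect, and even there most runs of the unadjusted model reject nothing. Hypothesis 1 proposes the reverse direction, with activity change predicting recovery. Then 3-month RMDQ is a mediator, and step 4 shows that adjusting for it removes a true total effect. This part of the objection stands in full: 3-month RMDQ cannot be a covariate in the only model.

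**Unused 3-month data.** Nor is the 3-month RMDQ left unused: it forms the primary outcome, and is only not named in the 1-year models.

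**Conclusion.** The mismatch between aims and analysis holds on the text alone and needs no assumption. Two 1-year models name one activity predictor each, while Objective 2 and Hypothesis 2 call for confounders to be addressed at 1 year. Followed as written, the plan gives unadjusted 1-year odds ratios and leaves Hypothesis 2 untested over that horizon. This should be corrected. It does not touch the 3-month primary analysis.

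The size of any bias is not established. The simulated range for ΔRT3, from slight to large, rests on correlations, a status effect and a prevalence that the documents do not give. Whether 3-month RMDQ confounds or mediates cannot be settled from the documents either. The missing-covariate point applies to both 1-year models; the 3-month-status point applies to ΔRT3 only.

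**What to change.** - **Both 1-year models:** report unadjusted and adjusted results, using a short covariate set fixed in advance and without p-value screening, for example baseline RMDQ, FABQ, GHQ12 and occupational activity.
- **Hypothesis 2:** show the activity coefficient with and without the psychosocial and occupational block.
- **Estimation:** use penalised (Firth) logistic regression, given the likely 18 to 36 people in the rarer outcome group.
- **ΔRT3 only:** add a further model with 3-month RMDQ, placed beside the baseline-adjusted model. Interpret it as the association remaining after 3-month recovery, and say that 3-month RMDQ may be a confounder or a mediator, so neither model alone settles the question.

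The cost is analysis wording, a little more analysis and somewhat wider intervals. No new data are needed.
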